### Participant timeline

Clusters were enrolled in March 2016 and randomized to trial arms in September 2016. Baseline recruitment and interviewing of women within study clusters began in October 2016 and was completed by January 2017. Distribution of materials to the MWHs and training of leaders and HEWs commenced in May 2017; upgraded MWHs were operational in June 2017. The endline assessments are scheduled to start in April 2019. An outline of the trial timeline is illustrated in Fig. 2.

**Fig. 2 Fig2:**
[figure not shown]
Tentative trial timeline. MWH maternity waiting home

In terms of participation in outcome assessments, women who are randomly selected for interviews at baseline and endline typically spend 25 min on average giving consent and about an hour for interviews.

### Sample size

Methods outlined by Hooper and Bourke [22] for parallel-arm, cluster-randomized trials with repeated cross-sections were used to calculate the sample size (see Additional file 1). Briefly, the methodology requires calculation of two design effects, with the product of the two used to inflate the sample size under individual randomization to account for within-period intracluster correlation coefficient (ICC) and the between-period ICC. The within-period ICC is the correlation between any two women in the same cluster and the same period, while the between-period ICC is the correlation between any two women in the same cluster but different periods.

The first design effect (d_c_) due to cluster randomization was calculated using a within-period ICC of 0.1 obtained from a review of community-based, cluster-randomized controlled trials in low-resource settings focusing on maternal health-care service outcomes [23]. The design effect was calculated as:
$$ {\mathrm{d}}_{\mathrm{c}}=1+\left(\mathrm{m}-1\right)\uprho $$where m is the cluster-period size (i.e. the number of women surveyed per PHCU in each round) and ρ is the within-period ICC.

The second design effect (d_r_) due to repeated assessments (baseline and endline) was calculated using both the within-period ICC and a cluster autocorrelation coefficient (π) of 0.8 to allow for a 20% decay of the correlation from within to between different periods [22]. We had no prior information to inform the cluster autocorrelation coefficient, but a 20% decay was considered reasonable. The second design effect was calculated as:
$$ {\mathrm{d}}_{\mathrm{r}}=\left(1-{\mathrm{r}}^2\right) $$where r = (mρπ)/d_c_.

The sample size assuming individual randomization was then multiplied by both design effects to arrive at a required sample size of eight PHCUs per arm with an average of 160 women per PHCU per round of survey, for a total sample size of 3840 for each survey (total women recruited = 7680). This sample size achieves 80% power to detect an absolute difference in the proportions of institutional births of 0.17 assuming a control arm proportion of 0.4 and using a two-sided alpha of 0.025 to account for two pairwise comparisons. The control arm proportion was obtained from JZHO data. An absolute difference of 0.17 is the smallest difference that can be detected, i.e. the difference between the weakest intervention (hypothesized to be the leader training intervention) arm versus control.

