### Primary analysis: effectiveness of the intervention components

Baseline characteristics of women will be tabulated by trial arm to provide an overview of the study population and to check for any notable imbalances. Characteristics of interest will include the age of women, the education levels of women, the distance between home and the nearest health centre, and household wealth. Means, standard deviations and ranges will be presented for continuous variables, while frequencies and percentages will be reported for categorical variables.

An intention to treat approach will be employed where random assignments of clusters to the three trial arms will be preserved regardless of adherence to the intervention assignment. The primary outcome will be analysed using a generalized linear mixed model with random effects for PHCU (cluster) and time, and fixed effects for time, time by trial arm interaction, and the stratification variables. The main effects for trial arm will be dropped to constrain differences between the arms at baseline as recommended by Hooper et al. [24]. With only two measurement points, it will not be possible to determine whether or not time has a more complex relationship with the outcome (quadratic or cubic) and therefore only a first-order term for time will be included. To account for the bias due to a small number of clusters, we will use the Kenward–Roger degrees of freedom approximation [25].

A logit link function will be used, and the outcome assumed to have a binomial distribution. Pairwise comparisons of adjusted least square mean differences will be made together with 97.5% confidence intervals to determine the effect of each intervention arm versus control.

Odds ratios will be calculated by taking the exponential of the relevant combinations of regression coefficients. The ICC and cluster autocorrelation coefficient for institutional births (primary outcome), antenatal care use, and postnatal care use will be calculated in STATA and reported on the proportions scale. Secondary outcomes will be analysed as described for the primary outcome.

Statistical tests and confidence intervals will be two-sided; between-group comparisons will be calculated and presented with 95% confidence intervals with the significance levels set at the 2.5% level.

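### Fixed 0.025 testing of the two primary comparisons is valid, but a Holm step-down would gain power at the same 5% family-wise error if both interventions work

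*Protocol article*

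**What the plan says.** The Sample size section of the protocol article sizes the trial with a "two-sided alpha of 0.025 to account for two pairwise comparisons". The stated target is 80% power for a difference of 0.17, "assuming a control arm proportion of 0.4", and the comparison behind it is the weaker one, expected to be leader training alone against control.

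The section headed Primary analysis: effectiveness of the intervention components carries the same level into the analysis. Comparisons of adjusted means are to be reported "together with 97.5% confidence intervals to determine the effect of each intervention arm versus control", and tests are to be judged "with the significance levels set at the 2.5% level". Neither section gives a step-down, hierarchical or other sequential rule.

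The last paragraph of the Background hypothesizes that both interventions raise institutional births, the combined arm by more.

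**The concern.** Under the fixed split, each comparison must reach 0.025 whatever the other shows. Once one null hypothesis has been rejected at 0.025, only one remains, and testing it at 0.05 still keeps the family-wise error within 5%. The fixed rule leaves that margin unused.

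Under the protocol's own hypothesis, the combined arm would usually pass first. The comparison still held to 0.025 would then be leader training against control, the one on which the trial was sized. With 24 clusters already randomized, the testing rule can still be made more efficient without adding clusters or women.

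**Working it through.** **Inputs from the Sample size section.** Control proportion 0.40; intervention 0.57; two-sided alpha 0.025; 80% power; within-period ICC 0.1; cluster autocorrelation 0.8; 160 women per cluster per survey; 8 clusters per arm.

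**Reproducing the stated size.**
- Individually randomized size: 163 women per arm (two proportions, no continuity correction).
- d_c = 1 + 159 × 0.1 = 16.9.
- r = (160 × 0.1 × 0.8) / 16.9 = 0.757, so d_r = 1 − 0.757² = 0.426. The product d_c × d_r is 7.205.
- 163 × 7.205 = 1174 women per arm, and 1174 / 160 = 7.34 clusters. This rounds up to 8, giving 1280 per arm and 3840 per survey, as stated.

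**Power at 8 clusters per arm, fixed 0.025.**
- Effective size per arm = 1280 / 7.205 = 177.6.
- Variance sum = 0.40 × 0.60 + 0.57 × 0.43 = 0.4851.
- Standard error = √(0.4851 / 177.6) = 0.0523, so the expected z is 0.17 / 0.0523 = 3.25.
- Normal power = Φ(3.253 − 2.241) = 84.4%. The pooled-variance version gives 83.6%.
- With a t reference on 20 df (assumed; the protocol plans Kenward–Roger degrees of freedom but gives no number), power is 79%.

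**Bonferroni against Holm.** I simulated 4 million pairs of test statistics with correlation 0.5, which follows from a shared control arm and equal allocation if the arm variances are treated as equal. Holm tests the smaller p-value at 0.025 and, if it is significant, the other at 0.05.

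| True differences | Quantity | Normal: Bonferroni → Holm | t, 20 df: Bonferroni → Holm |
|---|---|---|---|
| 0.17 and 0.17 | Power per comparison | 84.4% → 88.4% | 79.0% → 84.0% |
| 0.17 and 0.17 | Power to show both | 74.9% → 83.0% | 68.1% → 78.2% |
| 0.17 and 0.17 | At least one significant | 93.9% → 93.9% | 89.8% → 89.8% |
| Combined 0.22 (assumed), leader training 0.17 | Power, leader training | 84.4% → 89.9% | 79.0% → 86.5% |
| One at 0.17, the other 0 | Power for the effective arm | 84.4% → 84.6% | 79.0% → 79.1% |
| Both 0 | Family-wise error | 4.65% → 4.65% | 4.6% → 4.6% |

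With one true null, the chance of rejecting it is 2.5% under Bonferroni and about 4.4% under Holm, still within 5%.

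**Ceiling on the gain.** Even if the combined arm always passed, leader training could not exceed its power at 0.05: Φ(3.253 − 1.960) = 90.2% under the normal approximation.

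**The case against.** The case for leaving the plan alone has real force.

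- **The rule is valid and already paid for.** The test level, the sample size and the 97.5% intervals agree with one another. By the protocol's own method the rounded-up design gives about 84% against a target of 80%. A reader might infer from the 79% figure that the trial is underpowered, but that figure rests on an assumed 20 df and lies one point below target. The document does not support calling it a shortfall. This stands.
- **Holm is not the only route.** With a shared control, a single-step Dunnett test uses a critical value of 2.212 instead of 2.241, keeps matching simultaneous intervals and gives about 85%. Step-down Dunnett gives 88.6%, close to Holm's 88.4%. This stands; Holm's advantage is its simplicity and that it needs no assumption about correlation.
- **The gain depends on the other arm succeeding.** This stands, as the table shows. It is also the scenario that the protocol hypothesizes.
- **Tests and intervals part company.** Every extra rejection under Holm has p between 0.025 and 0.05, so its 97.5% interval from the same model includes no effect. This holds for all such rejections, not just some, and has to be disclosed. It does not cancel the gain, because the Holm test itself keeps the 5% bound.

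The analysis section also says that "between-group comparisons will be calculated and presented with 95% confidence intervals", which sits awkwardly with the 97.5% intervals two paragraphs earlier. That is a separate inconsistency, to be reconciled under either procedure.

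**Conclusion.** This is a cheap improvement, not a correction of an error. Replacing the fixed split with Holm adds about 4 to 5 points of power per comparison and about 8 to 10 points for showing both, when both differences are 0.17. If the combined effect is 0.22, leader training gains about 5 to 8 points.

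The figures rest on the protocol's ICC, autocorrelation and control proportion, on a correlation of 0.5 between the test statistics, and on the assumed 20 df and 0.22. A reader might also infer that Holm would justify a smaller trial. It would not: the chance of at least one significant result is unchanged, and the rest of the gain disappears if only one intervention works.

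**What to change.** In the Primary analysis section, before endline data are seen, state that for the two primary comparisons the smaller p-value is tested at two-sided 0.025 and, only if it is significant, the other at two-sided 0.05; otherwise testing stops. Leave the sample size statement as it is, since it is then conservative.

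Add three points on reporting:
- the Holm test decides significance;
- the 97.5% intervals are reported as simultaneous intervals, and the 97.5% interval of a comparison significant only at the second step will include no effect;
- 95% intervals are shown alongside, labelled as unadjusted.

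The cost is a few sentences of wording and the need to explain that mismatch if it arises. No clusters, women or data items are added.

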### Outcomes

The primary outcome is self-reported institutional birth defined as delivery of the last child at a health facility where obstetric care is provided (i.e. health centre or hospital) as reported by an enrolled woman. Births at home, en route to a facility or at a health post will not be considered an institutional birth.

Two other maternal health-care service outcomes will be assessed: 1) antenatal care and 2) postnatal care. Self-reported antenatal care received for last child delivered as well as the total number of antenatal care visits made will be assessed. Self-reported postnatal care received for the last child delivered within 48 h and 6 weeks will be assessed as secondary outcomes.

### Data collection and management

Data on outcomes and other variables of interest are collected through household surveys prior to intervention roll-out (baseline) and after 24 months of implementing the intervention (endline). Trained interviewers will conduct face-to-face interviews using structured questionnaires programmed onto tablet computers using Open Data Kit. Questionnaires contain sections on sociodemographics, reproductive history, maternal health-care service use, danger sign knowledge, attitudes towards maternal health-care services, awareness of/experience with MWHs, social support and health-related quality of life. Interviews are expected to last approximately 1 h and will be conducted in a quiet, private space at the homes of the women. If selected women are absent from their homes, interviewers will visit households up to three different days/times to attempt to interview them before the woman will be replaced with another randomly selected woman. Some demographic information will be collected from those women who refuse to take part in the trial if they agree to provide this data.

Data collected are submitted to a secure cloud server on a weekly basis from tablet computers. They are checked for inconsistencies and errors and these are communicated to field supervisors and brought to the attention of interviewers to avoid repetition and preserve data quality.

Qualitative data will be collected at baseline and at follow-up. Focus group discussions (with religious leaders and local community leaders) and key informant interviews (with HEWs and health facility staff) will be conducted to understand the roles stakeholders play in maternal and child health, what activities they engage in to promote safe motherhood and what their expectations and experiences are with respect to MWHs. As part of process monitoring, routine meetings held at the district and community level will be periodically attended over the course of the 24-month intervention period; data will be collected primarily using participant observation and field notes.

### Primary analysis: effectiveness of the intervention components

Baseline characteristics of women will be tabulated by trial arm to provide an overview of the study population and to check for any notable imbalances. Characteristics of interest will include the age of women, the education levels of women, the distance between home and the nearest health centre, and household wealth. Means, standard deviations and ranges will be presented for continuous variables, while frequencies and percentages will be reported for categorical variables.

An intention to treat approach will be employed where random assignments of clusters to the three trial arms will be preserved regardless of adherence to the intervention assignment. The primary outcome will be analysed using a generalized linear mixed model with random effects for PHCU (cluster) and time, and fixed effects for time, time by trial arm interaction, and the stratification variables. The main effects for trial arm will be dropped to constrain differences between the arms at baseline as recommended by Hooper et al. [24]. With only two measurement points, it will not be possible to determine whether or not time has a more complex relationship with the outcome (quadratic or cubic) and therefore only a first-order term for time will be included. To account for the bias due to a small number of clusters, we will use the Kenward–Roger degrees of freedom approximation [25].

A logit link function will be used, and the outcome assumed to have a binomial distribution. Pairwise comparisons of adjusted least square mean differences will be made together with 97.5% confidence intervals to determine the effect of each intervention arm versus control.

Odds ratios will be calculated by taking the exponential of the relevant combinations of regression coefficients. The ICC and cluster autocorrelation coefficient for institutional births (primary outcome), antenatal care use, and postnatal care use will be calculated in STATA and reported on the proportions scale. Secondary outcomes will be analysed as described for the primary outcome.

Statistical tests and confidence intervals will be two-sided; between-group comparisons will be calculated and presented with 95% confidence intervals with the significance levels set at the 2.5% level.

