## Background

The recently established Sustainable Development Goals reaffirm a global commitment to reducing maternal mortality [1]. Significant progress was made in reducing maternal mortality worldwide during the Millennium Development Goal period from 1990 to 2015; however, levels remain unacceptably high and large regional disparities exist. Globally, maternal mortality in 2015 was 216 per 100,000 livebirths, while in sub-Saharan Africa the rate was more than double this (546 per 100,000 livebirths). Ethiopia is one of the ten countries in the world that together account for almost 60% of all maternal deaths [2].

The majority of maternal deaths are preventable if women have timely access to good-quality maternal health-care services. Access to skilled obstetric care during and soon after birth is critical for the survival of women. However, in Ethiopia, only 26% of women who gave birth in 2016 reported doing so at a health facility [3]. In fact, over 40% of births were overseen by traditional birth attendants and in 15% women were entirely on their own [3]. Obstetric services are provided at the health centre and hospital level but are not available at community-based health posts.

Several barriers have been identified in rural sub-Saharan African that can impact a woman’s ability to access skilled obstetric care. These include barriers in the decision to seek care, barriers in reaching care, and barriers in receiving quality care once they arrive at a health facility, commonly referred to as the “three delays” [4]. Community-based interventions are often implemented to address the first two barriers [5–7], while the third barrier requires health system improvement on several levels [8].

Geographical and financial barriers are frequently cited as barriers to reaching skilled obstetric care during and after birth [9]. Women regularly have to travel large distances across difficult terrain, often made impassable during the rainy seasons, to get to health facilities [10]. Transportation options are frequently limited and may be expensive, leading to a limiting effect on the utilization of obstetric care [11]. Community-based surveys in Ethiopia report that women who live closer to health facilities are more likely to give birth there; for instance, women who are within a 1-h walking distance have 3.3 times higher odds of delivering at a health facility [12].

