### Trial design

This study is a parallel, three-arm, stratified, cluster-randomized controlled, superiority trial with 24 clusters. The trial arms are as follows: 1) upgraded MWH + leader training; 2) leader training alone; and 3) standard care. Primary health-care unit (PHCU) catchment areas were designated as clusters for the trial. PHCUs are composed of a health centre and satellite health posts; health posts operate in the community, covering a population of 3000–5000 and are each managed by two to three HEWs. MWHs are located within health centres as standalone structures or in the form of a room assigned to function as an MWH. Outcome assessments will be made using repeat cross-sectional surveys at baseline (prior to intervention roll-out) and at 24 months postintervention (i.e. the endline). A schematic for the trial design is displayed in Fig. 1. A cluster-randomized design was selected because the interventions are delivered at the health facility and community level which precludes individual-level randomization.

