### Cluster and individual selection

PHCUs were eligible for trial participation if health centres had a standalone MWH or a room designated for this purpose. All 26 health units in the three districts were eligible and 24 were randomly selected for the trial using a random number generator in STATA v13.

Women of reproductive age were eligible to participate in the trial if they were living in the villages within the selected PHCU catchment areas and had a pregnancy outcome (livebirth, stillbirth, spontaneous/induced abortion) up to 12 months prior to a survey round; baseline surveys commenced in October 2016 and endline surveys are scheduled to begin in April 2019. Lists of pregnant women registered by HEWs at health posts and Women’s Development Army volunteers within villages (‘*kebeles*’) function as the sampling frame for selection of eligible women at each survey time point. Names of women, their village of residence and their date of delivery organized by PHCU are included in the sampling frame. Random numbers generated in STATA v13 were assigned to each woman in the list, ranked, and then the required number sequentially selected. Since women were not excluded based on prior participation in surveys, it is possible that there is some overlap of participation in baseline and endline surveys, but the probability is expected to be low.

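### The primary model is valid but uses no woman-level covariate, and women are compared by arm only at baseline, so a case-mix difference arising at endline would be neither seen nor adjusted for

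*Protocol article*

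**What the plan says.** The section on the primary analysis of effectiveness lists the model terms: "random effects for PHCU (cluster) and time, and fixed effects for time, time by trial arm interaction, and the stratification variables". It adds that "The main effects for trial arm will be dropped to constrain differences between the arms at baseline". No characteristic of the individual woman is in the list, and the section names no covariate-adjusted sensitivity analysis.

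The same section plans one comparison of women by arm: "Baseline characteristics of women will be tabulated by trial arm to provide an overview of the study population and to check for any notable imbalances". On the content of that table it says "Characteristics of interest will include the age of women, the education levels of women, the distance between home and the nearest health centre"; wealth is the fourth item. It does not say what follows if an imbalance is found.

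Under Trial design, "Outcome assessments will be made using repeat cross-sectional surveys at baseline (prior to intervention roll-out) and at 24 months postintervention". Under Cluster and individual selection, the protocol says of women taking part twice that "it is possible that there is some overlap of participation in baseline and endline surveys, but the probability is expected to be low". That section makes lists kept by health extension workers and Women's Development Army volunteers the sampling frame. The section on local leader training names both groups among those to be trained. The Informed consent section confirms that clusters are randomised before either survey.

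The Background section reports from community surveys in Ethiopia that "women who are within a 1-h walking distance have 3.3 times higher odds of delivering at a health facility".

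**The concern.** The treatment contrast rests on the endline women. Nearly all of them are new, and they are sampled from April 2019, about 31 months after the September 2016 randomisation. Baseline women are also sampled after randomisation, but before roll-out in May 2017, so their lists cannot yet reflect the training. By endline, the people who keep the lists have been trained in two arms and not in the third. If trained list-keepers registered, for example, more remote women, the intervention arms would have a different mix of distances at endline. A table of baseline women cannot reveal that.

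Distance is a strong predictor by the protocol's own citation. The two stratification factors (functionality of the waiting home and emergency obstetric capacity) describe the facility and not the woman's access to it. The data needed to check and adjust are already collected. At stake is the robustness of the estimate to measured case mix and, possibly, some precision.

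**Working it through.** **1. The plan's own figure.** Inputs from the Sample size section: cluster-period size m = 160, within-period ICC ρ = 0.1, cluster autocorrelation π = 0.8, 0.40 v 0.57, two-sided alpha 0.025, power 80%.

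- d_c = 1 + 159 × 0.1 = 16.9
- r = 160 × 0.1 × 0.8 / 16.9 = 0.757
- d_r = 1 − 0.757² = 0.426; product of the two design effects = 7.205
- Individually randomised size: 163 per arm; 163 × 7.205 = 1,174 women, or 7.34 clusters, rounded up to 8. Total 8 × 160 × 3 = 3,840 per survey.

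The stated size reproduces. Normal-approximation power with 8 clusters is 83.6% (77.9% to 79.2% by noncentral t with 17 to 21 degrees of freedom). The effective size is 1,280 / 7.205 = 178 per arm, so the standard error of the arm difference is √((0.24 + 0.2451) / 178) = 0.052, or about 5.2 points.

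**2. Strength of distance.** Let q be the share of women living within a 1-h walk. The documents do not give it, so 30% to 70% is an assumption. Take the odds ratio as 3.3 and the overall proportion as 0.40, and solve (1 − q) × o/(1 + o) + q × 3.3o/(1 + 3.3o) = 0.40 for o, the odds among far women.

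| q | far | near | near − far |
|---|---|---|---|
| 0.3 | 0.314 | 0.601 | 0.288 |
| 0.5 | 0.261 | 0.539 | 0.277 |
| 0.7 | 0.217 | 0.478 | 0.261 |

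**3. Imbalance new at endline.** Nothing at baseline offsets it, so the shift is imbalance × (near − far). For 10 points: 0.10 × 0.261 to 0.10 × 0.288, or 2.6 to 2.9 points, which is 15% to 17% of the 17-point target. For 5 to 15 points of imbalance, the shift is 1.3 to 4.3 points (8% to 25%).

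**4. Imbalance present at both rounds.** With the arm main effect dropped, the estimate behaves on the linear scale like the endline difference minus r times the baseline difference. A persistent difference is therefore multiplied by 1 − 0.757 = 0.243. For 10 points with q = 0.5: 2.8 × 0.243 = 0.7 points, about 4% of the target.

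**5. How large might a new imbalance be?** If catchments do not change and listing does not differ by arm, only the sampling of women matters. The standard error of the difference in q is √(2 × 0.25 / 1,280) = 0.020. Ten points is about five such standard errors, so a new imbalance of that size would need a change in listing or in catchment composition.

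**6. Precision.** The documents give no adjusted ICC, so both scenarios are assumptions.

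| ICC after adjustment | Power, autocorrelation held at 0.8 | Power, only the stable part of the ICC falls |
|---|---|---|
| 0.10 (no change) | 83.6% | 83.6% |
| 0.08 | 89.8% | 84.7% (autocorrelation 0.06/0.08 = 0.75) |
| 0.05 | 97.1% | 88.2% (autocorrelation 0.03/0.05 = 0.60) |

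In the right-hand column the period-specific part stays at 0.1 × (1 − 0.8) = 0.02. That is the more natural case for distance, a stable feature of a catchment whose effect the baseline round already largely removes.

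**The case against.** The best reply is that nothing here is an error. Clusters are randomised, women are drawn from the lists by random number, and the model uses the stratification factors and the baseline round. It is a sound analysis of a cluster-randomised trial. An article may also leave a supplementary adjusted model and an endline table to the full protocol or analysis plan, neither of which is shown. That stands, and it limits the point to an improvement. The terms of the primary model, however, are spelled out, so leaving woman-level covariates out of it is a stated choice.

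Three stronger readings are tempting, and the documents support none of them.

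- **That chance imbalance with eight clusters per arm biases the result.** Such differences are between-cluster variation. The random effects and the Kenward–Roger degrees of freedom carry them into the interval, and the sample size allows for them. A shift of 2.8 points is about half of the 5.2-point standard error.
- **That baseline balance is uninformative about endline.** The same 24 catchments are surveyed at both rounds, and distance to a health centre is largely fixed geography.
- **That any distance imbalance goes in full into the estimate.** Step 4 shows that about three quarters of a persistent one is removed.

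The protocol also offers partial safeguards: effort to keep the lists complete, and a comparison of respondents with nonrespondents (Discussion). Neither compares endline women by arm, and a woman who was never listed is in neither group. That the lists will in fact differ by arm is a possibility and not something the documents show.

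**Conclusion.** The point holds as a low-cost improvement to a valid analysis. The gap is a specific one: a case-mix difference that appears between arms only at endline would be neither displayed by the planned table nor adjusted for in the planned model, and the training of the list-keepers in two arms gives a plausible route to it.

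The size is modest: about 2.6 to 2.9 points per 10 points of new imbalance, and about 0.7 points if the imbalance was there at baseline too. These figures assume that the cited odds ratio carries over to this population, that 30% to 70% of women live near, and that the design ICC and autocorrelation hold. The documents give no comparable predictor strength for age, education or wealth. A reader might also expect a large gain in power. That depends on the autocorrelation staying at 0.8 as the ICC falls; if only the stable part of an ICC of 0.10 is removed to reach 0.08, the gain is about one percentage point.

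**What to change.** Pre-specify distance to the nearest health centre, age, education and household wealth as fixed effects, using data from both rounds. Either put them in the primary model and keep the stratification-only model as a sensitivity analysis or, at minimum, name the adjusted model as a sensitivity analysis. Settle the choice and the coding of each covariate before endline data are seen. Tabulate the same characteristics by arm at endline as well as at baseline.

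The cost is some plan wording, a few model terms and one table; no new data are needed. The adjusted odds ratio becomes conditional on the covariates, so report a standardised risk difference beside it. Adjustment deals with measured case mix only. It does not correct selection on unmeasured factors, such as willingness to use a facility, and the report should say so.
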